## Abstract

The presented study protocol outlines a comprehensive investigation into the interplay among the human microbiota, volatilome, and disease biomarkers, with a specific focus on Behçet’s disease (BD) using methods based on explainable artificial intelligence. The protocol is structured in three phases. During the initial three-month clinical study, participants will be divided into control and experimental groups. The experimental groups will receive a soluble fiber-based dietary supplement alongside standard therapy. Data collection will encompass oral and fecal microbiota, breath samples, clinical characteristics, laboratory parameters, and dietary habits. The subsequent biological data analysis will involve gas chromatography, mass spectrometry, and metagenetic analysis to examine the volatilome and microbiota composition of salivary and fecal samples. Additionally, chemical characterization of breath samples will be performed. The third phase introduces Explainable Artificial Intelligence (XAI) for the analysis of the collected data. This novel approach aims to evaluate eubiosis and dysbiosis conditions, identify markers associated with BD, dietary habits, and the supplement. Primary objectives include establishing correlations between microbiota, volatilome, phenotypic BD characteristics, and identifying patient groups with shared features. The study aims to identify taxonomic units and metabolic markers predicting clinical outcomes, assess the supplement’s impact, and investigate the relationship between dietary habits and patient outcomes. This protocol contributes to understanding the microbiome’s role in health and disease and pioneers an XAI-driven approach for personalized BD management. With 70 recruited BD patients, XAI algorithms will analyze multi-modal clinical data, potentially revolutionizing BD management and paving the way for improved patient outcomes.

## Introduction

1

Human microbiome is the set of all the microorganisms that live in symbiosis with the human body, including bacteria, fungi, viruses and archaea. It has been found that, in a standard 70 kg male, bacteria are as numerous as somatic cells (Sender et al., 2016), but, due to their small dimensions, they contribute only 3% of the whole human body weight (Flint, 2012). Nevertheless, microbial communities are essential to keep the human body healthy. They synthesize some vitamins that our genes are not able to LeBlanc et al. (2013), help in the digestive processes (McConnell et al., 2008), teach the immune system how to recognize pathogens or cancer cells and even produce anti-inflammatory or anti-cancer compounds to defeat them (Nakkarach et al., 2021). The study of the human microbiome has demonstrated that microbial cell gene number in the human body are 150 times larger than our own genome (Zhu et al., 2010; Grice and Segre, 2012) and radically different collections of microbes have been found between different people. Scarce knowledge about what are the causes of these variations and what regulates them has been achieved. A very impactful issue is that no understanding on how the human microbiome modification has influence on wellness, conservation of health, starting and rise of diseases has been reached (Gilbert et al., 2018; Mandrioli et al., 2019). However, a correlation between changes in the microbiome, its metabolome and interaction with the immune, endocrine and nervous systems and the appearance of a wide spectrum of diseases [e.g., inflammatory bowel disease (Frank et al., 2007; Gevers et al., 2014; Ni et al., 2017), cancer (Kostic et al., 2013) or depressive disorders (Jiang et al., 2015; Zheng et al., 2016)] has been detected. This finding indicates the possibility of treating this kind of illness by manipulation of such a microbial community. Variations in human oral or intestinal microbiome and its volatilome can mirror host lifestyle and affect the levels of diseases biomarkers (Vernocchi et al., 2020). The comprehension of the relationships between host microbiome and phenotypes is of fundamental importance to understand health or disease states. Similarly, chemical characterization of human breath and the identification of volatile organic compounds (VOCs) patterns linked to a specific disease, can provide information on the health state of a patient and allow early diagnosis of chronic diseases or the monitoring of the patient’s health state along therapeutic follow-up. In fact, VOCs are final products of cellular metabolic processes and their nature and/or concentration in human breath change along with metabolic pathways when a pathologic state onsets (Mozdiak et al., 2019).

Data from human microbiome and breath are inherently complex, noisy and highly variable because several factors such as diet, sex, hormonal status, drugs, habits, etc. could affect them. So, non-standard analytical methodologies are needed to extract their clinical and scientific potential. Nowadays, a lot of Artificial Intelligence (AI) methods, such as Machine Learning (ML) or complex networks, are available to catch this complexity. In particular, AI methods use several layers of linear and/or non-linear calculating units to understand the data they manipulate and to learn “patterns” from the same data. This learning can be used to classify the observations or to make predictions on them (Hassabis et al., 2017; Amodeo et al., 2021). The specific AI model to be used is chosen according to its capability to maximize prediction accuracy but requires, on the other hand, an increased complexity of the model itself, that makes it less interpretable (Shaban-Nejad et al., 2021) (e.g., “black boxes”). To overcome these drawbacks, coming from more complex models, and to adapt ML utilization to clinical contexts, eXplainable Artificial Intelligence (XAI) techniques have been introduced, that provide explanations for decisions the algorithm takes and for the risk scores calculated for every subject studied. Such a gain in interpretability for the chosen model is converted in the possibility to understand the main reasons standing behind a prediction and to point out the factors that majorly affect clinical risk scores at individual level. This approach is perfectly placed in an innovative concept of Personalized Medicine that requires the help of AI techniques.

The target of the proposed study is the Behçet Disease (BD), also known as Silk Road disease, a rare, complex and multi-systemic chronic vasculitis, characterized by mucocutaneous, articular, vascular and ocular lesions and also by central nervous system (CNS) symptoms. The most recurring signs of this disease are relapsing genital and oral aphthae (that can also spread in the whole digestive tract), ocular pathologies (>50% of cases), arthralgia and/or arthritis (45% of cases), venous system vasculitis and thrombosis. If thromboses occur in the arterial system, they usually involve pulmonary vessels. Neurological signs (neuro-BD) are frequent (>20%); they often occur 1–10 years after the first symptoms, and include headache, hemiparesis, behavior alterations and sphincter dysfunctions. Nowadays, BD etiology is still not clear and cannot be traced back to a single root cause: the overactivation of the innate immune system, typical of this disease, seems to be caused by an altered T-cells homeostasis, but it is common thought that also some components of the human microbiome can promote an abnormal adaptive immune response, in presence of a favorable genetic background (Rodrìguez-Carrio et al., 2021). In fact, several studies have linked BD to an intestinal or oral microbiota dysbiosis: in particular, a decrease in number of butyrate-producing bacteria, associated to a lower level of butyrate in fecal samples of patients has been noted (Consolandi et al., 2015). As concerning gut, butyrate is involved in regulatory T cells differentiation (Furusawa et al., 2013) and in the release inhibition of pro-inflammatory cytokines (Weng et al., 2007). Low production of butyrate in patients suffering from BD may cause both reduced T-reg responses and T-cells immune-pathological responses activation, as suggested by the prevalence of T helper cells Th1 and Th17 in patients affected by BD (Alpsoy, 2016). Influencing intestinal microbiota, with factors such as the diet, can have a role in correcting intestinal dysbiosis and in reducing the severity of BD active phases. The evidence collected in the last decade highlight that adhering to dietary patterns which include high content of fibers can be linked to a better intestinal microbiota equilibrium; such a condition is favorable for short chain fatty acid (SCFA) producer bacteria and unfavorable for bacteria species associated to a pro-inflammatory pattern (Fu et al., 2020). Microbiota associated with dietary patterns rich in fibers was found to be positively correlated with high levels of SCFA (acetate, propionate, butyrate). Intestinal microbiota produces SCFA during indigestible polysaccharides (fibers) fermentation; these acid compounds have a well-documented protective role against several pathologies (Ho et al., 2018). To the best of our knowledge, a well-defined diet plan for BD does not exist, and the general advice is to follow a balanced diet and to maintain an ideal weight. Nevertheless, the just mentioned studies allow us to speculate that following a diet rich in fiber can correct intestinal dysbiosis, which is involved in the BD pathogenetic mechanism, and stimulate butyrate endogenous production from intestinal microbiota, bringing to a potential improvement of clinical manifestations.

Keeping all these evidence in mind, the proposed study is aimed to: (i) establish correlations between oral and intestinal microbiota, fecal and salivary volatilome, breath and phenotypic features of human hosts, affected by BD, active and/or in remission; (ii) identify, through cluster analysis methods of metabolites, different groups of patients affected by BD; (iii) identify some taxonomic units of oral and fecal microbiota and metabolic markers that majorly contribute to the prediction of different clinical outcomes (e.g., number of active mucosal lesions, remission following the Behçet Disease Current Activity Form (BDCAF)); (iv) identify, with XAI methods (Bellantuono et al., 2022), some personalized metabolic markers that, for each patient, contribute to the prediction of his/her clinical outcome (personalized medicine); (v) evaluate the effects of soluble fiber intake (inulin) on eubiosis/dysbiosis conditions of oral and intestinal microbiota and on endogenous production of butyrate; and (vi) establish correlations between eating habits and clinical outcome of patients.

## Methods and analysis

2

### Study design

2.1

The project we are going to propose will be performed in three different sub-activities. The first sub-activity includes a two-arm randomized study (duration: 3 months): patients in the control arm will keep on assuming the standard therapy while patients in the treatment arm will assume soluble inulin-type fructans (inulin 90% from *Cichorium intybus L.*; Farmalabor S.r.l., Canosa di Puglia, Italy), along with the standard therapy. At the starting of study and 3 months later, for each patient, the following samples and data will be collected:

samples for the assessment of oral/fecal microbiota;breath samples;clinical data such as Body Mass Index (BMI), disease duration, clinical phenotype and ocular, articular or mucocutaneous involvement;laboratory data such as Erythrocyte Sedimentation Rate (ESR) and C-reactive protein (CRP);information on breath components;information about eating habits, inviting patients to keep a food diary that can provide detailed descriptions on type and quantity of food and beverages consumed.

Furthermore, the second sub-activity will consist of:

analysis of volatilome in breath samples and microbiota in saliva and fecal samples;analysis of bacterial community taxonomic composition in fecal and saliva samples;chemical characterization of breath samples.

Volatile metabolites (volatilome) chemical characterization in breath samples will be determined through gas-chromatography coupled with mass spectrometry (GC–MS). For quality assurance in sampling phase and avoid any environmental contamination of breath samples, the end-tidal fraction of the exhaled breath will be collected by an automated device named Mistral (Predict srl) and directly transfer onto suitable adsorbent cartridges (Bio-monitoring steel tube, Markes International Ltd., UK) that will be preconditioned at 330°C for 30 min with pure helium (99.999%), analyzed to verify VOCs background level and properly stored at 4°C until use. Once collected onto the adsorbent cartridges, VOCs will thermally desorb and analyze by means a thermal desorber (UNITY-2, Markes International Ltd.) coupled with a gas chromatograph (GC 7890, Agilent Technologies) and a mass selective detector (MS 5975, Agilent Technologies). The analytical methodology for VOCs characterization in breath samples has been already optimized and validated in previously published studies (Di Gilio et al., 2020a,b). With the purpose to emphasize the chemical information related to human metabolomics and identify the most part of endogenous VOCs of interest (not exclusively those included in standard mix) a semi-quantitative analysis based on compound abundances will be performed. More specifically, the GC–MS chromatograms will be analyzed using the GC–MS post-run analysis software (Agilent Mass Hunter Qualitative Analysis-Agilent Technologies Ltd., Santa Clara, USA) integrating only the peaks with intensity higher than 5 times than baseline and VOCs compounds will be identified through spectral library matching (Compounds library of the National Institute of Standards and Technology, Gaithersburg, MD 20899–1070, USA) and through comparison with GC–MS chromatograms obtained by analysis of standard solutions of 44 VOCs (Ultra Scientific Cus-5997). Microbiota composition study will be performed through metagenetic analysis of rRNA16S gene (V3 and V4 regions). A negative control for sequencing will be included in the workflow of 16S amplification and library preparation, consisting of all the reagents included in the sample processing and without the sample, to ensure that no contamination took place. Libraries will be quantified using a Qubit fluorometer (Invitrogen Co., Carlsbad, CA, USA) and pooled, including the Phix control library, to an equimolar amount (4 nM final concentration). FastQ file quality will be assessed by using FastQC software and analyzed by using the QIIME2 dedicated pipeline^1^ microbiome platform (version 2020.8). Denoising will be computed with the q2-deblur QIIME plugin. Taxonomy will be inferred with the QIIME-compatible database Silva v.138 SSU, using an amplicon sequence variant (ASV) table based on error-corrected reads (Calabrese et al., 2022; Vacca et al., 2022, 2023). Finally, the last sub-activity is devoted to the implementation of XAI methods: the data obtained with the previous sub-activities will be analyzed with innovative AI methods. The aim will be to evaluate the conditions of eubiosis/dysbiosis and to identify potential microbial and metabolic markers linked to BD, to eating habits of patients and to a soluble fiber dietary supplement administration. The estimated project duration should be 18 months, including the enrollment time.

### Study population

2.2

The study will be conducted on patients with BD, active or in remission according to BCDAF, aged from 18 to 65, after having signed the informed consent for participating in the study and for assuming inulin. Exclusion criteria will include pregnancy and breastfeeding, serious concomitant diseases or instability conditions (such as autoimmune diseases, chronic viral infections, malignant cancers), recent myocardial infarction (MI), chronic liver diseases and inflammatory bowel diseases (IBD) and recent (last 6 months) or current participation to slimming programs or assumption of weight loss drugs.

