### Interventional method

2.3

The fiber dietary supplement will be administered randomly to half of the study patients, in open-label mode. The BD patients will receive either inulin supplementation or placebo. The participants were recommended to consume the powder during the breakfast by mixing it to 150 mL of warm water and then stirring up the powder until dissolved.

At the starting point and 3 months later, for each BD patients will be collected: samples for the assessment of oral/fecal microbiota, breath samples, BMI, disease duration, clinical phenotype and ocular, articular or mucocutaneous involvement and information about eating habits. Patients in the treatment arm will assume 5 g per day of inulin in addition to their ordinary diet and in a randomized order. The 5 g dose was chosen after considering the amounts of prebiotics that would be sufficient to induce positive and significant changes in the gut microbiota, but low enough to avoid adverse effects and minimize gastrointestinal discomfort (Bouhnik et al., 1999; Kolida et al., 2007).

All data obtained, will be analyzed with innovative AI methods, in order to evaluate the conditions of eubiosis/dysbiosis and to identify potential microbial and metabolic markers linked to BD, to eating habits of patients and to a soluble fiber dietary supplement administration.

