### Data analysis

2.8

Data collected by investigators will include volatilome, oral/fecal microbiota, body mass index (BMI), disease duration, clinical phenotype and ocular, articular or mucocutaneous involvement.

The microbiota can be characterized in three different ways: alpha diversity metrics, relative abundance of phylotypes for each specimen and community state types (CST). Alpha diversity metrics, which represent the variety and richness of organisms in a specimen, and relative abundance of microbes will be analyzed through supervised machine learning algorithms as Random Forest or XGBoost classifiers. Supervised machine learning is a category of machine learning where the algorithm is trained on a labeled dataset, which means that each example in the training data is associated with the correct output or target. The algorithm learns to make predictions or decisions based on input data by generalizing from the labeled examples it has seen during training. Moreover, the XAI algorithm “SHapley Additive exPlanations” (SHAP) will be used to detect for each patient, which features are more important for the ML algorithm in its classification (Bellantuono et al., 2023; Novielli et al., 2023). SHAP is an algorithm used in machine learning to explain the predictions made by complex models, particularly for models like XGBoost, Random Forest, neural networks, and others. It provides interpretable explanations for individual predictions, helping users understand why a particular prediction was made. The third characterization, i.e., CST, which groups samples according to the composition of the microbiota, will be analyzed through the application of complex networks (CN). This mathematical method, also known as complex systems or complex networks theory, is a branch of network science that studies systems characterized by a large number of interconnected components or nodes, and the patterns and properties that emerge from these connections. In our case, interactions between microbiome and its host are complex phenomena, and to better understand this kind of complex interactions and to map microbiome behavior is of fundamental importance to have the possibility to model these interactions through CN. Modules of this complex biological network are key organizational elements for the network itself. To detect modular organizational structures of a complex network, community detection unsupervised algorithms will be used.

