### Anticipated results

3.2

This will be the first study that tries to understand the complex relationships between diet, intestinal microbiota and human breath in patients affected by BD through an innovative approach based on AI methods (Golob et al., 2023; Novielli et al., 2023; Papoutsoglou et al., 2023). Such an understanding can represent a significant step forward toward the comprehension of pathogenetic mechanism at the basis of BD onset and the identification of microbial, metabolic and immunological factors and therapeutic biomarkers able to control treatment outcome and to better understand how the such a treatment can modify microbiome. In fact, intestinal dysbiosis has been linked to inflammatory diseases (Douzandeh-Mobarrez and Kariminik, 2019) and recent studies have demonstrated that therapeutic treatment in rare rheumatological diseases can modify subclinical intestinal inflammation and dysbiosis (Manasson et al., 2020), highlighting the bidirectional nature of this correspondence. Furthermore, this study will evaluate for the first time with multivariate models if microbiome and breath modulation through the diet can improve disease activity in patients with BD under treatment. This analysis could enable us to find valuable markers to identify responders and non responders, allowing treatment optimization and a personalized therapeutic approach. This study could be also useful to analyze diet effects on BD activation and/or remission. Going into details, network approach thought for this study is aimed to catch functional structure of dynamic processes happening between microbiome and human host, to identify the coexistence of different microorganisms, to trace relationships between microorganisms and to identify cohesive groups that play fundamental roles in maintaining functional relationships in the global network during the treatment. Identification and quantification of some of the topological properties of the network modules can provide important information on microbiome interactions and on their relationship with possible disorders and anomalies in inflammatory and pathological states. Specifically, co-occurrence patterns and identified polymicrobial interactions will be related with other clinical and phenotypical data to detect correlations between network functional and structural properties and biological and pathological profiles in different starting conditions. This integrative approach is completely innovative, since it will allow to highlight some connectivity patterns linked to inflammatory states, pathologies, etiological agents and even the organisms responsible for pathology transmission.

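### Drugs are named as drivers of the microbiome and breath data, but section 2.2 bars only weight-loss drugs and programmes, and no data list shown names medication

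*Protocol article*

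**What the plan says.** The Introduction explains why microbiome and breath data are noisy: "several factors such as diet, sex, hormonal status, drugs, habits, etc. could affect them". Section 3.2 adds that "therapeutic treatment in rare rheumatological diseases can modify subclinical intestinal inflammation and dysbiosis".

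Background treatment continues in both arms. Section 2.1 states that "patients in the control arm will keep on assuming the standard therapy", and the treated arm adds inulin to the same therapy. The drugs that make up standard therapy are not specified. Section 2.2 admits patients with active disease and patients in remission.

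Among the exclusions in section 2.2, the only one that concerns a drug or a dietary exposure is "recent (last 6 months) or current participation to slimming programs or assumption of weight loss drugs". The others are pregnancy, breastfeeding and concomitant disease.

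Three places list the data to be collected:
- Section 2.1: "clinical data such as Body Mass Index (BMI), disease duration, clinical phenotype and ocular, articular or mucocutaneous involvement", with microbiota and breath samples, ESR, CRP and a food diary.
- Section 2.3: "samples for the assessment of oral/fecal microbiota, breath samples, BMI, disease duration, clinical phenotype and ocular, articular or mucocutaneous involvement and information about eating habits".
- Section 2.8: "Data collected by investigators will include volatilome, oral/fecal microbiota, body mass index (BMI), disease duration, clinical phenotype and ocular, articular or mucocutaneous involvement".

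Section 2.4 foresees multivariate models for adjustment and does not name the covariates.

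**The concern.** The article identifies drugs as something that moves its main measurements, but its eligibility text does not act on this for the exposures closest to the intervention. Inulin is a prebiotic and the sample size rests on microbial beta-diversity. Even so, nothing in section 2.2 keeps out a patient who has just finished antibiotics or who already takes a prebiotic or probiotic.

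The stake differs by aim. Aim (v), the effect of inulin, is a randomised comparison. Aims (i) to (iv) and (vi) are correlations, clusters and predictors of clinical outcome, which randomisation does not protect. If patients with active disease take different drugs from those in remission, a taxon or volatile compound moved by a drug can look like a marker of disease. SHAP shows which features a model used. It cannot separate a drug effect from a disease effect.

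**Working it through.** **Step 1: named drivers against the text that should handle them.** No stated figure in the article bears on this point, so the main check is a comparison of passages.

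| Item | Where it is named | How the shown text handles it |
|---|---|---|
| Diet | Introduction | Food diary in 2.1, eating habits in 2.3 |
| Drugs, rheumatological treatment | Introduction, 3.2 | No item in 2.1, 2.3, 2.8 or Table 1 |
| Weight-loss drugs and programmes | 2.2 | Excluded, with a 6-month window |
| Antibiotics, probiotics, other prebiotics | Not named | No exclusion in 2.2, no data item |

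The exclusion list is specific enough to set a 6-month window for one drug class, and it does not mention the classes in the last row.

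**Step 2: illustration with correlations.** All path values are assumptions. Let a therapy variable correlate *a* with disease activity and *b* with a taxon, with no direct link between taxon and activity. The spurious correlation is r = a × b. The chance that it is significant at two-sided 0.05 is about Φ(atanh(r) × √(n − 3) − 1.96). The sample sizes are the planned 70, and 56 after the article's 20% dropout (70 × 0.8 = 56).

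- a = b = 0.5: r = 0.25. For n = 70, 0.2554 × √67 − 1.96 = 0.13, giving 55%. For n = 56, 0.2554 × √53 − 1.96 = −0.10, giving 46%.
- a = b = 0.4: r = 0.16. For n = 56, 0.1614 × √53 − 1.96 = −0.79, giving 22%.
- a = b = 0.6: r = 0.36. For n = 56, 0.3769 × √53 − 1.96 = 0.78, giving 78%.

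**Step 3: second illustration, by simulation.** A taxon unrelated to activity is shifted by a drug whose use differs between active and remission patients. The set-up is 35 against 35, a two-sample t-test and 20,000 runs per setting. The equal split and the usage rates are assumed. The 0.8 SD shift is set equal to the article's design effect size. The spurious mean difference is the shift times the difference in use, for example 0.8 × (0.60 − 0.20) = 0.32 SD.

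| Drug use, active v remission | Shift 0.5 SD | 0.8 SD | 1.2 SD |
|---|---|---|---|
| 40% v 40% | 5% | 5% | 5% |
| 50% v 30% | 7% | 10% | 14% |
| 60% v 20% | 13% | 24% | 42% |
| 80% v 20% | 23% | 47% | 76% |

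The entries are the percentage of samples significant at 0.05. With equal use the rate stays at its nominal 5%, which is the position of the randomised comparison in expectation. The excess appears only when use differs between the groups compared, and its size follows the assumed imbalance.

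**The case against.** The strongest reply is that this is a journal article whose lists are plainly abbreviated. BDCAF, the Krause score and SF-36 are outcomes in Table 1, yet none of the three data lists names them. ESR and CRP are in 2.1 but not in 2.3 or 2.8. Sex is named as a driver in the same sentence as drugs and appears in no list, and nobody would conclude that it goes unrecorded. This stands. A reader might infer that the trial does not record medication. The documents do not support that, because the full protocol may well include it.

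A reader might also infer that the information would be lost for good. That does not follow either. Follow-up is at a single university rheumatology unit (section 2.7), so prescribed Behçet therapy may be recoverable from the chart. Antibiotics prescribed elsewhere and over-the-counter supplements are less certain.

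Three further objections are partly right:
- The article does not say that therapy differs with disease activity. The confounding is therefore conditional on that.
- Section 2.4 plans adjusted models, and the food diary may capture some fibre products. Neither helps with a drug exposure unless that exposure is available to the model.
- Section 2.5 puts the primary focus on separating the two arms, where randomisation balances background drugs in expectation.

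The eligibility text is less easily excused. Its wording is also open, but exclusion criteria are what a protocol article does state, and this list is detailed.

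**Conclusion.** The point holds in a limited form and should be acted on. As written, section 2.2 admits patients whose microbiota may already be altered by antibiotics, probiotics or another prebiotic, although the article itself names drugs as a driver. The data lists shown do not name medication, which is a gap in the text and not proof of a gap in the trial.

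It would be wrong to read this as bias in the inulin comparison. Randomisation protects that comparison, and the cost is added noise and a diluted contrast. The risk of misleading results lies in aims (i) to (iv) and (vi), and only if therapy differs with disease activity or outcome. The documents do not allow its size to be derived. The illustrative rates, from 7% to 78% wherever an imbalance was assumed, reflect their inputs and are not estimates for this trial.

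**What to change.** - **Section 2.2:** add current use of another prebiotic or probiotic as an exclusion, and state how recent antibiotic users are handled. The look-back period is for the investigators to set.
- **Sections 2.1, 2.3 and 2.8:** list Behçet therapy class and antibiotic, probiotic and fibre-supplement use at both visits. If the full protocol already records these, a line in each section is enough.
- **Non-randomised aims:** use baseline therapy class as a covariate in the correlation, cluster and outcome-prediction analyses. Keep to a few broad classes, because 70 patients support few extra terms and section 2.9 already warns of overfitting.
- **Arm comparison:** keep it on all randomised patients. A sensitivity analysis may exclude on baseline exposure only. Dropping patients for therapy changes or antibiotic use after randomisation would condition on events that inulin, or knowing the allocation in an open-label trial, could influence, and so could introduce bias.

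The cost is a short addition to the case report form, a few candidates excluded in a rare disease, and a few extra model terms.
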